## Abstract

**Background:**

Breastfeeding is recognized internationally as the most scientific and effective way to feed infants and young children. According to the World Health Organization in 2022, the exclusive breastfeeding rate within 6 months is 34.1% in China, which is still far from the goal of “more than 60% exclusive breastfeeding rate of infants within 6 months” by 2030 required by China’s State Council. It is necessary to promote breastfeeding and provide maternal breastfeeding guidance to increase exclusive breastfeeding. Factors influencing breastfeeding can be explained by the society ecosystems theory, distributed in macro, mezzo and micro systems. The interventions focused on breastfeeding promotion are mainly carried out in the health systems and services, home and family environment, community environment, work environment, policy environment or a combination of these facilities. But there is sparse research on integrating resources in the macro, mezzo and micro systems of maternal breastfeeding processes to promote breastfeeding behavior. A randomized controlled trial will test the effect of a breastfeeding promotion intervention model based on the society ecosystems theory versus usual prenatal and postnatal care on maternal and infant health and the exclusive breastfeeding rate at 6 months.

**Methods/design:**

The study is a single-blind, parallel design, randomized controlled trial with an intervention group (n = 109) and a control group (n = 109) that compares the effect of a breastfeeding promotion intervention model based on the society ecosystems theory with usual prenatal and postnatal care. The intervention covers macro- (policy, culture), mezzo- (family-hospital-community) and micro- (biological, psychological and social) systems of the maternal breastfeeding process. Infant feeding patterns, neonatal morbidity and physical and mental health of antenatal and postpartum women will be collected at baseline (28 to 35 weeks of gestation), 1-, 4-, and 6-month postpartum.

**Discussion:**

This is a multifaceted, multifactorial, and multi-environmental breastfeeding promotion strategy to help mothers and their families learn breastfeeding knowledge and skills. The study provides a new modality for adding breastfeeding interventions to prenatal and postnatal care for healthcare providers in the hospital and the community.

*Trial registration*: Chinese Clinical Trial Registry at www.chictr.org.cn, ChiCTR2300075795.

## Background

Breastfeeding is recognized internationally as the most scientific and effective way to feed infants and young children. *Global strategy for infant and young child feeding*, jointly published by the World Health Organization (WHO) and the United Nations International Children’s Emergency Fund (UNICEF), clearly stated that breast milk is the most optimal food for infants and young children [1]. Infants and young children should be exclusively breastfed until 6 months of age to maintain optimal growth and development.

The exclusive breastfeeding (EBF) rate is an important indicator to measure the breastfeeding status of a country or region. According to WHO global breastfeeding data [2], the EBF rate of infants under 6 months is 40%. Only a few countries in the world have EBF rates of more than 60%. The EBF rate within 6 months in developing countries is 36% and 34.1% in China [3], with obvious regional differences. In the *Outlines for Children’s Development in China (2021–2030)*, it is clearly stated that the goal is a “more than 50% EBF rate of infants within 6 months” [4], and the *National Nutrition Plan (2017–2030)* proposed reaching 60% by 2030 [5]. In 2021, the National Health Commission of the People ‘s Republic of China and 15 other departments jointly issued the *Government action plan promoting breastfeeding(2021–2025)* [6]. According to the plan, by 2025, the awareness rate of breastfeeding core knowledge in maternal and child families should be reach more than 70%, which indicates that a low breastfeeding rate is a public health problem related to maternal and infant health, and the public’s ideological concept should be taken into account to popularize the core knowledge of breastfeeding [6]. Therefore, it is necessary to promote breastfeeding and provide maternal breastfeeding guidance to increase the EBF rate.

The interventions focused on breastfeeding promotion are mainly carried out in the health systems and services, home and family environment, community environment, work environment, policy environment or a combination of any of these facilities [7, 8]. Sinha et al. found that interventions delivered in a combination of settings by involving health systems, home and family and the community environment concurrently seemed to have higher improvements in breastfeeding rates [8]. The Baby-friendly Hospital Initiative (BFHI) is a key component of the WHO/UNICEF Global Strategy for Infant and Young Child Feeding [9], which plays a technical guidance role in the intervention [8, 10]. Adherence to the BFHI Ten Steps has a positive impact on short-term, medium-term and long-term breastfeeding outcomes [9].

China has a relatively complete medical service system. Community health centers (CHCs), such as the primary medical and health institutions in this system, can provide convenient and quick medical and health services for residents and achieve the maximum rational allocation of limited medical resources. In addition, community health service centers in China are required to provide family-based comprehensive care that integrate prevention, medical treatment, rehabilitation and health education for vulnerable groups such as women and children within the community [11]. Community support appears to be essential for sustaining breastfeeding impacts of the BFHI in the longer term [9]. This reflects that the community can play a major role in breastfeeding core knowledge and skills promotion [12].

In Chinese tradition, maternal and infant care is mainly completed by mothers or mothers-in-law in addition to husbands, and the attitudes and behaviors of husbands and other family members towards breastfeeding largely influences maternal breastfeeding behaviors, and the role of family members in breastfeeding promotion cannot be ignored [13, 14]. Breastfeeding interventions involving family members effectively increase the EBF rate and improve breastfeeding knowledge and breastfeeding attitude [15, 16].

Breastfeeding educational interventions are also an important approach to promote breastfeeding and provide assistance for women to learn about breastfeeding in advance. A systematic review and meta-analysis found that interventions provided by lecture combined with practical skills effectively reduced breast engorgement and improved the EBF rate [17]. The optimal delivery time, format and structure of the interventions have been suggested as being provided during the antenatal to postnatal period; multicomponent group education and individual breastfeeding counselling and telephone follow-up [8]; both individual and group based; and having ≥ three sessions [18]. In addition, peer counselling has been found as the most promising strategy associated with higher rates of EBF [19].

An Internet-based mobile health information platform, benefiting from its information sharing and diversity of intervention forms, provides a good channel for implementing health education and health guidance [20]. It is also conducive to carrying out personalized breastfeeding health education, improving maternal breastfeeding knowledge and skills, improving breastfeeding attitudes, reducing the rate of weaning during infancy, and increasing the rate of long-term EBF [21, 22]. But at present, Internet-based breastfeeding interventions employing e-technologies should consider improving interactions with mothers and personalizing the content of the proposed interventions [23].

Therefore, it is necessary to construct a multifaceted, multifactorial, and multi-environmental breastfeeding promotion strategy to help pregnant women and their families learn breastfeeding knowledge and skills. According to the society ecosystems theory (SET) proposed by Zastrow [24], the author regarded the individual as a subject who develops and adapts through the interaction with various factors of the environment, and he classified the social-ecological system of the individual into three levels: micro, mezzo and macro systems. Micro system refers to an individual, which entails biological, psychological, and social systems of pregnant women in this study. Mezzo system refers to any small group, including family, work groups and other social groups. For example, hospitals, communities and families are important places for women throughout pregnancy, delivery and the postpartum period. Macro system refers to a system larger than a small group, which focuses on the social, political, and economic conditions and policies that affect people’s overall access to resources and quality of life. In the current study, this refers to the policies, institutions and culture as they relate to breastfeeding. These three systems are interrelated, mutually restrictive and influential, and all exist in the social environment. From the micro, mezzo and macro levels, efforts should be made to construct the ecological environment of breastfeeding recognition in society. The theory model applicable to breastfeeding is shown in Fig. 1.

**Fig. 1 Fig1:**
[figure not shown]
Diagram of society ecosystems theory model applied to breastfeeding

Therefore, it is necessary to optimize the existing breastfeeding promotion intervention program and construct a breastfeeding promotion intervention program to correct the public’s perception of breastfeeding, increase breastfeeding self-efficacy and improve breastfeeding behavior, thus increasing the EBF rate and improving maternal and infant outcomes. The current study addresses to the need for an effective breastfeeding promotion intervention program that is Internet-based and that addresses the three major barriers of the micro, mezzo and macro systems regarding breastfeeding behavior.

## Methods

### Aim

This study aims to compare the effect of a breastfeeding promotion intervention model based on the SET versus a usual prenatal and postnatal care program on the EBF rate at 6 months and breastfeeding duration; on improving maternal breastfeeding attitudes, knowledge, and self-efficacy; and on improving maternal and infant health.

### Study design and setting

The study is a single-blind, parallel design, randomized controlled trial with an intervention group (IG) and a control group (CG) allocated with a 1:1 randomization ratio that compares the effect of the breastfeeding promotion intervention model based on the SET, which is an IG, with a usual prenatal and postnatal care group, which is a CG (Fig. 2). This research will be conducted from August 2023 to April 2024 in Wuhan, China. Pregnant women will be recruited from August to October 2023 by convenience sampling at the Department of Obstetrics of Hubei Province Maternal and Child Health Hospital. The study protocol in compliance with the Declaration of Helsinki was approved by the Ethics Committee of Medical Research Committee of Medical College of Wuhan University (WHU-LFMD-IRB2023050) and the Hubei Province Maternal and Child Health Hospital (2023IEC070). It has registered in the Chinese Clinical Trial Registry at www.chictr.org.cn (registration number: ChiCTR2300075795).

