### Eligibility criteria

Women who are aged 18 to 36 years, 28 to 35 weeks of gestation, singleton pregnancy, with basic literacy skills and no barriers to communication and able to use a smartphone will be recruited. Participation will be voluntary and informed consent will be obtained; participants can withdraw from the study at any time with no prejudice. Women with serious contraindications to breastfeeding, such as acute infectious diseases, infection with acquired immune deficiency syndrome, syphilis, mammary gland insufficiency, breast surgeries such as mastopexy; or serious mental illness are excluded.

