#### Primary outcome

Breastfeeding rate is the primary outcome in this study. The infant feeding patterns are collected at 1-, 4- and 6-months postpartum. The breastfeeding rate and EBF rate at 1-, 4-, and 6-months postpartum are also calculated.

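### The stated study end of April 2024 falls before the last 6-month postpartum assessments, which the recruitment window and entry gestation push to about late July 2024

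*Protocol article*

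**What the plan says.** Study design and setting gives the calendar: "This research will be conducted from August 2023 to April 2024 in Wuhan, China", and "Pregnant women will be recruited from August to October 2023". Eligibility criteria sets entry at "28 to 35 weeks of gestation". The abstract's Methods/design paragraph says that the measures "will be collected at baseline (28 to 35 weeks of gestation), 1-, 4-, and 6-month postpartum", and Primary outcome repeats the schedule: "The infant feeding patterns are collected at 1-, 4- and 6-months postpartum".

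The 6-month point carries the trial. The Aim compares the groups "on the EBF rate at 6 months and breastfeeding duration", and Sample size is worked out for EBF at 6 months: 34.1% versus 60%, two-sided 0.05, 90% power, at least 76 per group, 218 in total (109 per group in the abstract). Nothing in the text gives a later end of follow-up. The flow chart (Fig. 2) was not available for this check.

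**The concern.** Follow-up is counted from birth, but recruitment is during pregnancy. The time from a woman's entry to her last assessment is therefore the rest of her pregnancy plus 6 months. From the end of October 2023, April 2024 allows only the 6 months and leaves no time for the remaining pregnancy.

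If the stated period were followed literally, many women would have no 6-month feeding status, and the comparison the trial was sized for would rest on far fewer women than planned. The extra women allowed for loss to follow-up and withdrawal would be used up by the calendar alone.

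**Working it through.** **Inputs from the protocol article.** Recruitment August to October 2023, taken as 1 August to 31 October. Gestation at entry 28 to 35 weeks (upper limit read as 35+0 or 35+6). Last assessment 6 months postpartum. Study end April 2024, read generously as 30 April. Rates 34.1% and 60%, two-sided 0.05, 90% power, 76 per group, 109 per group after inflation.

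**Assumptions not in the article.** Gestation at delivery (37 to 42 weeks tried), recruitment dates spread evenly over the window, and gestation at entry spread evenly over 28 to 35 weeks.

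**Step 1: the plan's own sample size.** With P = (0.341 + 0.60)/2 = 0.4705, the article's formula gives

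n = [1.960 × √(2 × 0.4705 × 0.5295) + 1.2816 × √(0.341 × 0.659 + 0.60 × 0.40)]² / 0.259² = (1.3835 + 0.8736)² / 0.06708 = 75.9, so 76 per group.

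Then 76 × 1.2 × 1.2 = 109.4, or 109 per group and 218 in total. The stated figures reproduce. The problem is the calendar.

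**Step 2: 6-month dates.** 6-month date = recruitment date + (weeks at delivery − weeks at entry) + 6 months.

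| Recruited | Weeks at entry | Weeks at delivery | Birth | 6 months |
|---|---|---|---|---|
| 1 Aug 2023 | 35 | 40 | 5 Sep 2023 | 5 Mar 2024 |
| 15 Aug 2023 | 28 | 40 | 7 Nov 2023 | 7 May 2024 |
| 31 Oct 2023 | 35 | 40 | 5 Dec 2023 | 5 Jun 2024 |
| 31 Oct 2023 | 28 | 40 | 23 Jan 2024 | 23 Jul 2024 |
| 31 Oct 2023 | 28 | 37 | 2 Jan 2024 | 2 Jul 2024 |
| 31 Oct 2023 | 28 | 42 | 6 Feb 2024 | 6 Aug 2024 |

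A 6-month assessment by 30 April 2024 needs a birth by about 30-31 October 2023, when recruitment closes. Even a woman recruited on 31 October at 35+6 who delivers at 37 weeks (8 November) reaches 6 months only on 8 May 2024. No delivery assumption from 37 to 42 weeks fits the whole cohort into the stated period.

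**Step 3: share affected if collection closed on 30 April 2024.** I counted every combination of recruitment day and day of gestation at entry, equally weighted. The ranges cover the two readings of 35 weeks. Counting 6 months as 183 days or as calendar months moves them by about one percentage point.

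| Delivery at | Without 6-month status | With it | Per arm, of 109 |
|---|---|---|---|
| 40 weeks | 62-65% | 35-38% | about 38-41 |
| 39 weeks | 54-58% | 42-46% | about 46-50 |
| 38 weeks | 47-50% | 50-53% | about 55-58 |
| 37 weeks | 39-43% | 57-61% | about 62-66 |

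Deliveries at 41 and 42 weeks are worse (about 69-72% and 76-79% without it). The inflation from 76 to 109 can absorb a loss of 33/109 = 30% per arm. Every row exceeds that before any ordinary attrition.

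**Step 4: power.** Inverting the article's formula, power = Φ[(0.259√n − 1.3835)/0.6817], where 0.6817 = √(0.341 × 0.659 + 0.60 × 0.40).

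- n = 38: (1.5966 − 1.3835)/0.6817 = 0.313, power about 62%.
- n = 53: (1.8855 − 1.3835)/0.6817 = 0.736, power about 77%.
- n = 66: (2.1041 − 1.3835)/0.6817 = 1.057, power about 85%.
- n = 76: 90%, as planned.

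**The case against.** The strongest reply is that the loss is conditional. The article says when the research is conducted. It does not say that data collection or analysis stops in April 2024, and the visit schedule applies to every woman. The likeliest explanation may be a wrong date: October 2023 plus 6 months is April 2024, as if follow-up ran from recruitment rather than birth. April could also mark the end of intervention delivery. Table 1 ends the intervention at one month postpartum, which for the last woman delivering at 40 weeks is 23 January plus one month, or 23 February 2024 (6 March at 42 weeks). This stands, and it means the shortfall cannot be asserted as fact. It does not remove the conflict between the stated dates, because both explanations are guesses and the text gives no other end date.

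Three stronger readings are tempting, and the article does not support them.

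- **That most women would lack the endpoint.** This holds under the even-spread assumptions with delivery at 39 weeks or later. It is about half or just under at 38 weeks and fails at 37. Front-loaded recruitment, or entry mostly late in gestation, would also reduce the loss. The article gives neither the pace of recruitment nor gestation at delivery.
- **That the women retained would be a biased or under-treated set.** An April cut-off would keep early recruits and those entering late in gestation. But Tables 1 and 2 give everyone the same structured antenatal content: policy and facility material in week 1, and four lectures completed before delivery. Only the open-ended elements would run for less time before birth. Date and gestation at entry precede random allocation, so the cut-off does not in itself bias the comparison between arms.
- **That the registry record carries the same error, or that a missing database-lock rule is a defect.** The registry entry is not shown, and lock rules are commonly left to fuller documents.

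**Conclusion.** The concern holds as a contradiction between dates that the article itself states. With recruitment to 31 October 2023 from 28 weeks, the last 6-month assessment falls on about 23 July 2024 with delivery at 40 weeks (2 July at 37 weeks, 6 August at 42). An end in April 2024 cannot contain it, and this conclusion needs no assumption about how recruitment is spread.

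The size of the loss does rest on assumptions: closure on 30 April, even recruitment, even gestation at entry, and a common week of delivery. Under these, between about two fifths (37 weeks) and two thirds (40 weeks) of women would lack the endpoint. Power would be about 62% at the low end (38 per arm), 77% at 53 and about 85% at the high end (66), all before other losses. Quoting only the lowest figure would overstate the case. Because it concerns the endpoint on which the trial was sized, the point is more than a clerical slip. It can be settled by correcting one date. The sample size calculation is not affected.

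**What to change.** Reconcile the dates in Study design and setting. Keep the recruitment window and the 1-, 4- and 6-month schedule, and change the stated end of follow-up to the last expected 6-month assessment: late July to early August 2024, plus the visit window. Say that the 6-month analysis is run only after that assessment. If April 2024 was meant as the end of something else, such as intervention delivery, label it so and give the end of follow-up separately.

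The cost is a corrected date and a finish three to four months later than stated. No visits beyond those already scheduled are needed, and the endpoint and sample size stay as they are.

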**Fig. 2 Fig2:**
[figure not shown]
Research flow chart. *IIFAS* Iowa Infant Feeding Attitude Scale, *BKQ* Breastfeeding Knowledge Questionnaire, *BSES-SF* Breastfeeding Self-efficacy Seale Short Form, *EPDS* Edinburgh Postnatal Depression Scale, *SSRS* Social Support Rating Scale, *PAQ* Pregnancy-Related Anxiety Questionnaire, *PSAS-CN* Postpartum Specific Anxiety Scale-Chinese Version

### Eligibility criteria

Women who are aged 18 to 36 years, 28 to 35 weeks of gestation, singleton pregnancy, with basic literacy skills and no barriers to communication and able to use a smartphone will be recruited. Participation will be voluntary and informed consent will be obtained; participants can withdraw from the study at any time with no prejudice. Women with serious contraindications to breastfeeding, such as acute infectious diseases, infection with acquired immune deficiency syndrome, syphilis, mammary gland insufficiency, breast surgeries such as mastopexy; or serious mental illness are excluded.

### Sample size

The current EBF rate for infants under 6 months of age in China is 34.1% [3]. After the intervention, the rate is expected to increase to 60%, which was required by the *National Nutrition Plan (2017–2030)* [5]. Sample size was calculated for EBR in 6 months for a two-sided hypothesis test with a power of 90% and a significance level of 0.05. Therefore, according to the following formula, the study requires a minimum sample size of 76 (each group). Considering a 20% lost follow-up rate and 20% withdrawal rate because of failure to participate in the full intervention due to prematurity, a total of 218 participants will be needed for the study.$${n}_{1}={n}_{2}=\frac{{{[u}_{\alpha }\sqrt{2P\left(1-P\right)}+{u}_{\beta }\sqrt{{P}_{1}\left({1-P}_{1}\right)+{P}_{2}\left({1-P}_{2}\right)} ]}^{2}}{{(P1-P2)}^{2}}$$

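### The 109 women per arm do not preserve the required 76 after the stated 20% and 20% losses; applied to both arms, those losses leave 65 to 70 and about 85% to 87% power, not 90%

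*Protocol article*

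**What the plan says.** All of the following is in the protocol article, mainly under Sample size.

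- Control rate: "The current EBF rate for infants under 6 months of age in China is 34.1"%.
- Intervention rate: "After the intervention, the rate is expected to increase to 60"%, a national policy target.
- Test: "Sample size was calculated for EBR in 6 months for a two-sided hypothesis test", "with a power of 90% and a significance level of 0.05".
- Result of the printed formula: "the study requires a minimum sample size of 76 (each group").
- Allowance for losses: "Considering a 20% lost follow-up rate and 20% withdrawal rate". The withdrawals are attributed to women who, because of prematurity, do not take part in the whole intervention.
- Conclusion: "a total of 218 participants will be needed for the study". The Methods/design part of the Abstract confirms the split: "an intervention group (n = 109) and a control group (n = 109").

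The step from 76 to 109 is not shown. Study design and setting gives 1:1 allocation. Statistical analysis states that the trial will be analysed per protocol.

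**The concern.** The section calls 76 per group a minimum and then names two sources of loss. The number randomised should therefore be large enough that 76 remain once both have occurred. To retain 76, one divides by the fraction retained; multiplying by one plus the loss rate always gives too few. A total of 218 looks like the result of multiplying.

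Both losses count here. Under a per-protocol analysis, a woman who withdraws without completing the intervention leaves the analysed sample just as one lost to follow-up does.

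At stake is the stated power. If the trial finds no difference, readers will judge that result against a claimed type II error of 10%, when the plan's own attrition figures imply more.

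**Working it through.** **1. Reproduce the plan's figure.** Inputs from Sample size: P1 = 0.341, P2 = 0.60, two-sided α = 0.05 (u = 1.960), power 90% (u = 1.2816). The mean rate is P = (0.341 + 0.60)/2 = 0.4705.

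- √[2P(1−P)] = √0.49826 = 0.7059
- √[P1(1−P1) + P2(1−P2)] = √0.46472 = 0.6817
- n = (1.960 × 0.7059 + 1.2816 × 0.6817)² / 0.259² = 5.095 / 0.06708 = 75.95, so 76 per arm.

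This agrees with the protocol.

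**2. Ways of getting from 76 to a number randomised.**

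| Method | Per arm | Total |
|---|---|---|
| 76 × 1.2 × 1.2 | 109.4 → 109 | 218 |
| 76 × 1.4 | 106.4 → 107 | 214 |
| 76 / (0.8 × 0.8), losses in succession | 118.75 → 119 | 238 |
| 76 / 0.6, losses added | 126.7 → 127 | 254 |

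Of these, only the double multiplication gives 218. Division for a single 30% loss, 76/0.7 = 108.6, would also round to 109, but the section states no such rate.

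**3. What 109 per arm can absorb.** 76/109 = 0.697, so at most 30.3% may be lost. The stated rates imply 1 − 0.8 × 0.8 = 36% in succession, or 40% added.

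**4. Evaluable women per arm, losses in both arms.**

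- In succession: 109 × 0.64 = 69.8, about 6 below 76.
- Added: 109 × 0.60 = 65.4, about 11 below 76.

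**5. Power.** Solving the protocol's formula for power gives Φ{[0.259√n − 1.960 × 0.7059] / 0.6817}.

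| n per arm | Argument of Φ | Power |
|---|---|---|
| 76 | 1.283 | 90.0% |
| 69.8 | 1.144 | 87.4% |
| 65.4 | 1.043 | 85.2% |

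Exact binomial power of the uncorrected χ² test tells the same story: 89.3% at 76, 87.7% at 70 and 83.9% at 65.

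**6. In terms of effect.** To regain 90% power at 69.8 or 65.4 per arm, the intervention rate would have to be about 61.1% or 62.0% rather than 60%.

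**7. If withdrawals occur in the intervention arm only.** The control arm keeps 109 × 0.8 = 87.2. The intervention arm keeps 69.8 or 65.4. Power is then 90.6% or 89.6%.

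**The case against.** The strongest reply is that the second 20% belongs to the intervention arm alone. The section ties it to not completing the intervention, and the Control group section says controls receive nothing further from the researchers after the first contact, so a control woman has no intervention to leave. On that reading power is 89.6% to 90.6%, essentially as stated. Equal enlargement of both arms does not refute it, because 1:1 allocation would produce equal arms anyway.

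This reading is possible and makes the power claim conditional. It does not rescue the section as written. The withdrawal rate follows directly on a per-group minimum and is not limited to one arm. Even on this reading the intervention arm ends with 65 to 70 women, below the minimum set for each group. Removing women for prematurity from one arm only would also upset the randomised comparison, so the authors would need to state and defend it.

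Two further points are fair. The double multiplication by 1.2 is inferred, since the step is not printed; the shortfall in numbers does not depend on it. And the loss of power is small beside the uncertainty in the 60%, which is a policy target rather than an estimate. That limits the weight of the point but does not make the stated figure right.

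**Conclusion.** The concern holds. The figure of 76 per arm is correct, but 109 per arm does not retain it at the stated loss rates.

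With both losses in both arms and a per-protocol analysis, about 70 women per arm remain (losses in succession) or 65 (losses added). Power is 87.4% or 85.2%, which is 2.6 to 4.8 points below the stated 90%; type II error rises from 10% to about 13% or 15%. These figures take the plan's rates of 34.1% and 60% as given.

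If the withdrawal rate was meant for the intervention arm only, the loss of power largely vanishes, but that arm still misses its minimum and the text must say so. The error is real and modest. It should be corrected because the minimum, the two loss rates and the total cannot all stand as written.

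**What to change.** Keep 218 and correct the statement. First say whether the 20% withdrawal rate applies to both arms or to the intervention arm only, and whether it is taken after the loss to follow-up or added to it. Then give the power that follows. If it applies to both arms, suitable wording would be: *With 109 women randomised per arm, 20% loss to follow-up and 20% withdrawal, about 65 to 70 per arm will be evaluable, giving 85% to 87% power to detect 34.1% versus 60%.* Print the inflation step so that it can be checked.

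The cost is one or two sentences, no additional participants, and a slightly less favourable power figure. If the authors prefer to hold 90% with losses in both arms, the total becomes 238 (20 more women) or 254 (36 more).
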